### Patient measures

Table 3 provides details on planned patient measures and timing of administration. Participants complete a survey at baseline, two months, and six months after enrollment. Participants complete the surveys over the telephone with research assistants. We make 10 attempts over one month to reach participants to complete the surveys. The surveys include a demographics questionnaire designed by the study team; a smoking behavior and history questionnaire designed by the study team; the BASIS-24 scale measuring recent mental health functioning [22]; an impulsivity scale [23]; a functional health literacy scale [24]; measures of readiness to quit, motivation, self-efficacy, and attitudes about smoking developed by the study team; and satisfaction with treatment received from the TeleQuitMH program.

**Table 3 T3:** Patient measures and assessment schedule

**Measures**	**BL**	**2m**	**6m**
Sociodemographics	X		
Current and historical smoking behavior	X	X	X
Readiness to quit	X	X	X
Quitting self-efficacy and motivation	X	X	X
Medication assessment: Current use, contraindications to NRT or Bupropion	X		
Use of prior smoking cessation treatment	X	X	X
Nicotine dependence	X	X	X
Alcohol and substance abuse	X	X	X
Smoking environment: Social support for quitting, household smokers, household smoking rules, employer smoker rules	X		
Attitudes about smoking	X		
Mental health symptoms (BASIS-24)	X	X	X
Health literacy	X		
Impulsivity	X		
Patient satisfaction with the program		X	X
Patient assessment of treatment fidelity/counseling content		X	X

*BL* = baseline; *2m* = two months after enrollment; *6m* = six months after enrollment.

### Formative/implementation evaluation

The study includes a formative evaluation to help us modify the care coordination program and implementation strategies during our study period, to enhance the interpretation of summative data, and to better inform future implementation efforts. Table 4 provides details on formative evaluation activities and measures. We used the Stetler et al. [25] model to guide the development of our formative evaluation methods. This model identifies four stages of formative evaluation for implementation research:

1. ***Developmental phase****—*Based on our experience with the primary care-based projects, we anticipate that it will take six months to implement the TeleQuitMH program at a site. This time includes identifying a local champion, obtaining Institutional Review Board approval, implementing the TeleQuitMH program’s main components, and informing providers. During this time we will conduct mental health provider surveys and interviews with site stakeholders to measure 1) the level of organizational readiness of the participating clinics both in general and specific to the intervention, 2) perceptions of the evidence supporting smoking cessation telephone counseling and smoking cessation medications, 3) perceptions regarding the feasibility and utility of the planned intervention, and 4) perceptions of anticipated barriers or facilitators to the successful implementation of the intervention. We will also assess the extent to which each site’s local champion and Clinical Advisory Committee are interested in, and actually perform, their project responsibilities, assess the structure and processes of the site’s state quitline operations (e.g., hours of operation), and assess the type and intensity of local smoking cessation services already available to mental health patients. We will formulate modifications to the TeleQuitMH program structure and our provider outreach/marketing efforts to address findings from these activities.

2. ***Implementation****/****progress****-****focused phase****—*For the purpose of our evaluation, we will combine Stetler et al.’s *implementation* and *progress-focused* phases. After implementing the TeleQuitMH program at a site, we assess several patient and provider variables on a regular basis, including the number of patient referrals, the percentage and types of providers who are referring patients, the percent of patients enrolling and engaging in treatment, and patient satisfaction with the program. We also conduct a second provider survey during this phase evaluating reasons for a provider’s referring or not referring patients to the program, provider satisfaction with various aspects of the program, and what, if any, recommendations providers have for changes to the program that they feel would improve its effectiveness. We also assess referral trends in relation to our provider outreach activities in order to modify or target future outreach efforts. Last, we continue to assess the impact of each site’s TeleQuitMH components (e.g., prescribing structure, referral process) on implementation fidelity, referral rates and patient uptake, treatment fidelity by the VA counselors, and the presence and quality of facilitation provided by the local champions and Clinical Advisory Committees.

3. ***Interpretation****/****sustainability****-****focused phase****—*Following the intervention period at each site, we collect two additional measures: an organizational survey of mental health programs, which assesses each site’s mental Health clinic structure, size, staffing, environment, and resources [26]; and mental health unit performance rates on the mental health treatment and tobacco use clinical reminders required by the VA [27]. We use these data and the formative evaluation data collected during the previous two phases to describe the local implementation context, to formulate interpretations of primary outcomes data, and to create recommendations for future implementation efforts of the telephone care coordination program.

**Table 4 T4:** Formative evaluation (FE) measures and evaluation schedule

**FE Measure/ activity**	**Measure/activity description**	**Develop-mental**	**Impl./ progress focused**	**Interpret./ sustainability focused**

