### Clinical intervention: telephone care-coordination program

The TeleQuitMH care coordination program consists of the following sequential elements. The program begins with a provider-level intervention that enables the referral of patients to tobacco cessation treatment. After the referral, patient-level treatment intervention begins.

1. ***Simple EMR referral****—*The care coordination program takes advantage of VA usual care that requires providers to screen patients for tobacco use and either provide them with counseling or refer them to treatment during routine visits. We are not attempting to standardize the screening process or counseling given by mental health providers. Our study introduces a new treatment referral option for providers—that of referring patients to TeleQuitMH via a new electronic consult in the EMR. Providers have the option to confirm the patient’s contact information and enter free-text information about their patient in the consult screen, but these responses are not required. Providers can access the consult either through the consult menu or through the tobacco use clinical reminder screens.

2. ***Proactive outreach***—Once our program receives a referral, we mail the patient a welcome packet that includes information about the TeleQuitMH program and study and a brochure containing all elements of informed consult. One week following this mailing, program staff call the patient using the phone number in his or her medical record. Staff make five attempts over two weeks to reach referred patients by phone to discuss the smoking cessation program, offer enrollment, and complete the verbal informed-consent process. Patients who enroll in treatment are provided with the next four elements of the program described below. Patients not interested in treatment have the opportunity to enroll in the follow-up surveys only.

3. ***Medication coordination***—All enrolled patients can receive mailed smoking cessation medications unless they decline or have contraindications noted by their referring provider. The method with which the TeleQuitMH program provides medications varies by site and is determined by a site Clinical Advisory Committee formed before site implementation. This committee consists of key stakeholders from the departments of Psychiatry, Social Work, Psychology, Pharmacy, and Smoking Cessation. There are three prescribing methods from which the Clinical Advisory Committee can choose:

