#### Strategy 3: informatics support

The PRECEDE model posits that enabling interventions simplify the implementation of a recommended practice for providers. To enable the use of TeleQuitMH, we create a local electronic consult for the program that allows providers to refer patients with three-to-four extra clicks as they complete a regular clinical progress note in the EMR system. The consult is also attached to the tobacco clinical reminder and mental health assessment templates in the EMR system, with which providers are already familiar. For providers who do not have clinical privileges to send consults, the study’s project director also accepts referrals via secure email.

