**MH Unit Data on Implementation Context**				
VA Survey of MH Programs[28]	Clinic’s structure, size, staffing, environment, and resources for meeting MH and tobacco cessation treatment goals.			**X**
MH Unit Performance Data[29]	Clinic-level performance on VA MH and tobacco performance measures			**X**

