#### Interpretation/sustainability phase

After the intervention period has ended at each site, we will use the *interpretation/sustainability phase* of our formative evaluation to interpret primary outcomes, using qualitative pattern-matching approaches to explore how the implementation activities and structure of the implementation (including treatment fidelity) may help explain variations in outcomes at the site level. Similarly, data on the implementation context will be analyzed to determine variation across sites and whether that variation is associated with both the nature of the implementation and the outcomes achieved. Formative evaluation data will be analyzed longitudinally to determine if changes in implementation are associated with changes in process variables (e.g., reach, uptake). In terms of sustainability, analyses will focus on identifying the site and implementation features and characteristics that facilitated and hampered effectiveness. Finally, descriptions of the degree to which core elements of TeleQuitMH were integrated into systems of care at each site will be used to characterize the sustainability of TeleQuitMH and to identify the local conditions which facilitate replication and dissemination.

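### Tobacco reminder performance is treated as site context but scheduled only after a program that altered that reminder, so its association with referral and uptake may be partly circular

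*Protocol article*

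**What the plan says.** **Timing.** In the Protocol article, Formative/implementation evaluation, the account of the last phase reads: "Following the intervention period at each site, we collect two additional measures". The first is a survey of how mental health programs are organized. The second is "mental health unit performance rates on the mental health treatment and tobacco use clinical reminders required by the VA". Table 4 describes the second as "Clinic-level performance on VA MH and tobacco performance measures" and marks both measures in the interpretation/sustainability column only.

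**Role.** Table 4 places both under "MH Unit Data on Implementation Context". The Interpretation/sustainability phase paragraph of the analysis section says that context will be examined for variation across sites and for "whether that variation is associated with both the nature of the implementation and the outcomes achieved".

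**Link to the program.** The clinical intervention section says that VA usual care "requires providers to screen patients for tobacco use and either provide them with counseling or refer them to treatment during routine visits". Strategy 3 (informatics support) adds: "The consult is also attached to the tobacco clinical reminder and mental health assessment templates in the EMR system". The Reach section likewise refers to the tobacco reminder as adapted for TeleQuitMH.

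**The concern.** A context variable should describe the setting that the program entered. Here the tobacco reminder rate is collected after the program has run, on a reminder that the program changed, and a referral is one of the two ways to meet the underlying requirement. If TeleQuitMH consults count toward the rate, a site that refers many patients can show a higher rate because it refers many patients. Relating that rate to referral, reach or uptake would then partly relate a quantity to itself.

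At stake is Objective 1, which carries equal weight with the clinical aims in a Type II hybrid. Its context findings feed the recommendations for future implementation. Good tobacco performance could be read as a condition that helps uptake when it is partly a result of uptake.

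**Working it through.** **1. The plan's own figures.** The article gives no figure for reminder performance. The one relevant input is the expected referral rate of 25% (Participants). It is consistent with the enrollment target: the Table 1 smokers sum to 4,500 + 3,900 + 5,000 + 2,300 + 1,800 + 2,000 = 19,500, and 19,500 × 0.25 × 0.50 = 2,437.5, against a stated total of about 2400.

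**2. The passages side by side.**
- The measure has no developmental-phase entry in Table 4, so no pre-launch value is scheduled.
- Table 4 labels it context, and the analysis section relates context to implementation and outcomes.
- EMR modification and provider referrals are themselves scored implementation activities (Table 5, items 4 and 7), so the variables on the other side of the association include what may move the rate.
- Table 4 also defines exposure to TeleQuitMH by completed tobacco screening, which lies close to the same reminder.

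**3. How far the rate could move.** Let p be performance without the program, r the referral rate, and k the extent to which referrals fall on patients whose reminder would otherwise be unmet. With k = 0, referrals only replace counseling that already met the reminder. With k = 1, they are spread independently of whether it was met.

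Post-period rate = p + (1 − p) × r × k

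The values of p and k are assumptions; r = 0.25 is from the article. At k = 1:
- p = 0.50: 0.50 + 0.50 × 0.25 = 62.5%
- p = 0.70: 0.70 + 0.30 × 0.25 = 77.5%
- p = 0.90: 0.90 + 0.10 × 0.25 = 92.5%

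At k = 0 nothing moves. Two sites that both start at 70% but refer 10% and 40% (assumed) would end at 73% and 82% when k = 1: a 9-point difference in apparent context where there was none.

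**4. Built-in correlation.** Suppose p and r are unrelated across sites, with assumed between-site SDs s_p and s_r. To first order,

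corr(post-period rate, r) ≈ k(1 − p)s_r / √{[k(1 − p)s_r]² + [(1 − kr)s_p]²}

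For p = 0.70, r = 0.25, k = 1 and both SDs 5 points: 0.30 × 5 = 1.5 and 0.75 × 5 = 3.75, so 1.5 / √(2.25 + 14.06) = 0.37. Simulation gives the same value. Simulated correlations for mean p = 0.70 and mean r = 0.25, pooled over all simulated sites:

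| s_p (points) | s_r (points) | k = 0 | k = 0.5 | k = 1 |
|---|---|---|---|---|
| 3 | 5 | 0 | 0.27 | 0.55 |
| 3 | 10 | 0 | 0.50 | 0.80 |
| 5 | 5 | 0 | 0.17 | 0.37 |
| 5 | 10 | 0 | 0.32 | 0.62 |
| 10 | 5 | 0 | 0.09 | 0.20 |
| 10 | 10 | 0 | 0.17 | 0.37 |

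Over mean p of 50%, 70% and 85%, the k = 1 values run from 0.11 (p = 85%, s_p = 10, s_r = 5) to 0.91 (p = 50%, s_p = 3, s_r = 10). By construction, the pre-launch rate p has correlation 0 with referral in every case.

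**The case against.** The other side has real points, and most of them stand.

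- **The rate is undefined.** The article gives neither its numerator nor its window. A reader might infer that the rate is in fact raised by TeleQuitMH referrals. The documents do not show this. They show that referral is one way to meet the usual-care requirement and that the consult sits in the reminder. A referral may only replace counseling that already counted, and then the effect is nil.
- **Date of collection is not period covered.** Routine rates can be extracted later for an earlier window, and a condensed article may leave the window to the full protocol. That stands. If a pre-launch window is already specified there, stating it settles the point.
- **Much context is measured before launch.** A reader might infer that all site context is post-intervention. It is not. Readiness, existing cessation services, quitline operations, champion and committee, provider survey and stakeholder interviews all fall in the developmental phase, and the late measures are used together with the earlier data. None of these, however, is a pre-launch tobacco reminder rate.
- **No mechanism for the other measures.** Nothing suggests that referrals change clinic structure, staffing or resources, or the mental health treatment reminders. The point does not extend to them.
- **Limited consequence.** Site differences are explored by qualitative pattern-matching over six sites, with no correlation test specified, and the Discussion concedes that the effectiveness of the implementation strategies cannot be determined. This limits the harm but does not remove it: pattern-matching cannot by itself separate a cause of uptake from a result of uptake.

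**Conclusion.** The point holds in a narrow form. Of the two measures that Table 4 heads as mental health unit context, the tobacco reminder rate is scheduled only after the intervention, is to be related to implementation and outcomes, and can be raised by the program's own referrals. Its association with referral, reach and uptake may be partly circular.

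The size cannot be determined from the documents. Under the assumed inputs the built-in correlation lies between 0 and about 0.91. It rests on the assumed baseline rate, between-site spread and degree of replacement, and on TeleQuitMH consults counting toward the rate.

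A reader might extend the point to the abstinence results. That is not supported. Abstinence among enrollees shares no definition with the reminder rate, so at most there is possible reverse influence. The randomized Aim 3 comparison does not use the rate. Nor is the matter beyond repair later, provided the routine pre-launch data still exist. This is an inexpensive improvement to the Objective 1 context analysis, not a demonstrated error.

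**What to change.** 1. State the definition of the tobacco reminder rate and the calendar window it covers.
2. For each site, extract the rate for a fixed window before the consult was activated (for example, the preceding 12 months). Use that value as context in the Interpretation/sustainability phase analyses.
3. Report the post-period rate and the pre-to-post change as a process outcome, not as context.
4. Amend the Table 4 row to match. The program organization survey can stay where it is.

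The cost is one further extraction of routine performance data and a table edit, assuming the pre-launch data are retained. No patient contact or new instrument is needed.

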**Reach/Implementation Analysis**				
Referral rates	Number of patients referred on weekly and monthly basis.		**X**	**X**
Treatment uptake	Percent of referred patients enrolling in treatment, engaging in treatment, and completing treatment.		**X**	**X**
Exposure to TeleQuitMH	Percent of MH patients for whom tobacco use screening was completed.			**X**
**Patient Process Data**				
Enrollment Rates	Rates of enrollment to TeleQuit MH and State quitlines		**X**	**X**
TeleQuitMH Satisfaction	Self-reported satisfaction with TeleQuitMH structure and treatment (including VA versus quitline satisfaction) ; assessed 2m and 6m after enrolling		**X**	**X**
**Provider Process Data**				
Provider Survey	Perceptions of program marketing; how likely they will be to use the program; barriers to implementation; suggestions for improvement; provider use of the program; program satisfaction; perceived effectiveness of activities to facilitate implementation; impact of the program on their patients/client.	**X**	**X**	**X**
Stakeholder Interviews	Perceptions of program marketing; how likely they will be to use the program; barriers to implementation; suggestions for improvement; provider use of the program; likes/dislikes about the program; impact of the program on their patients/clients.	**X**	**X**	**X**
Referral rates/patterns	Percent of providers referring; Number of referrals from each provider; Rates by provider type		**X**	**X**
**MH Unit Data on Implementation Context**				
VA Survey of MH Programs[28]	Clinic’s structure, size, staffing, environment, and resources for meeting MH and tobacco cessation treatment goals.			**X**
MH Unit Performance Data[29]	Clinic-level performance on VA MH and tobacco performance measures			**X**
**Implementation Facilitation - Structure**				
Site Champion	Presence of a site champion, level of interest in performing site champion duties, position at the VA, role on the project	**X**	**X**	**X**
Site Clinical Advisory Committee	Presence of a site Clinical Advisory Committee, level of interest in performing Committee duties, Committee members positions at the VA & roles on the project	**X**	**X**	**X**
Site smoking cessation services	Presence, types, and structure of site smoking cessation clinic and other local smoking cessation services	**X**		**X**
TeleQuitMH Structure	Structure of the TeleQuitMH program at each site, including design and appearance of the tobacco cessation clinical reminder, prescribing structure, and referral mechanisms (e.g., consult design, email referral option)	**X**	**X**	**X**
State quitline Structure/Issues	Structure of quitline services; issues/problems identified in connecting TeleQuitMH patients to quitline services.	**X**	**X**	**X**
IRB Issues	Time from first submission to receiving IRB approval; type of submission required (full board review, expedited, exempt); site-specific requirements that may affect TeleQuitMH implementation and adoption (e.g., detailed consent process)	**X**		**X**
**Implementation Facilitation - Activities**				
Marketing Efforts	Provider outreach efforts, academic detailing, provider feedback.		**X**	**X**
Treatment Fidelity	Extent to which the TeleQuitMH staff are providing the telephone counseling, medication coordination and warm-transfer to the state quitlines as intended.		**X**	**X**

*MH* = mental health.

### Summative analyses

We are using the RE-AIM framework to guide summative data analyses [28]. The RE-AIM framework suggests that it is crucial for a system-level intervention to consider the following: *Reach*—the proportion of patients reached by the intervention; *Effectiveness*—the effectiveness of the program at meeting clinical goals; *Adoption*—the proportion of providers and patients that used the intervention; *Implementation*—the extent the intervention was implemented; and *Maintenance*—whether the intervention was maintained over time.

#### Reach

To assess the reach of the intervention, we will determine the proportion of mental health patients who were exposed to the TeleQuitMH program. To do this, we will first use the EMR system to identify all smokers at participating facilities who had a mental health visit during the intervention period. This group—all smokers with a mental health visit—will be our denominator. If the TeleQuitMH-adapted tobacco use clinical reminder appeared for the patient’s mental health care provider, we will consider that patient to have been exposed to TeleQuitMH. *Reach* will be calculated as the number of smokers exposed to TeleQuitMH divided by the total number of smokers with a mental health clinic visit.

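### Exposure to TeleQuitMH has two different definitions, and the one used for Reach can class a referred or enrolled smoker as not reached

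*Protocol article*

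**What the plan says.** Summative analyses introduces Reach in general terms as "the proportion of patients reached by the intervention". The Reach section then makes it operational. On the denominator it says: "This group—all smokers with a mental health visit—will be our denominator". On the numerator, the test is whether the adapted tobacco reminder came up for the mental health provider; if it did, "we will consider that patient to have been exposed to TeleQuitMH". The ratio is the "number of smokers exposed to TeleQuitMH divided by the total number of smokers with a mental health clinic visit". No other way of becoming exposed is given.

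Table 4, under its Reach/Implementation Analysis block, has a row named Exposure to TeleQuitMH, described as "Percent of MH patients for whom tobacco use screening was completed".

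Referral does not depend on the reminder. The section on the clinical intervention states: "Providers can access the consult either through the consult menu or through the tobacco use clinical reminder screens". Strategy 3 adds that the consult is attached to mental health assessment templates. For providers without the privilege to send consults, the "project director also accepts referrals via secure email".

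**The concern.** There are two problems.

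- **Two rules for one measure.** A reminder appearing to a provider and a tobacco screen being completed are different events. The clinical intervention section describes screening as something VA usual care already requires, and says the study does not try to standardize it. A high screening figure could therefore arise with no program activity.
- **A gap in the Reach rule.** Because referral has several routes and exposure has only one, a smoker can be referred and enrolled yet fall outside the exposed group.

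Reach is one of the five summative RE-AIM outcomes, and the Background describes a Type II hybrid that gives implementation and clinical outcomes equal priority. The section on the interpretation/sustainability phase plans to relate changes in implementation to process variables and gives reach as an example. Table 4 also records reminder design and referral mechanisms, including the email option, as features of each site. If the share of referrals without a display differs by site, the misclassification would differ by site too, and would disturb those comparisons.

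**Working it through.** **Step 1. The two definitions side by side.**

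- Reach section: the numerator is smokers for whose provider the adapted reminder appeared. The denominator is smokers with a mental health visit in the intervention period.
- Table 4: the numerator is patients with completed tobacco screening. The denominator is mental health patients.

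The numerators are different events. A reminder can appear and be left uncompleted, and a screen can be completed where the program's reminder played no part. The denominators also differ as written, but this carries less weight: the Reach section itself opens by speaking of mental health patients before narrowing to smokers, so Table 4 may be using the same shorthand.

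**Step 2. Inputs for the size of the gap.**

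- N = 19,500 smokers a year (Participants). The Table 1 estimates agree: 4,500 + 3,900 + 5,000 + 2,300 + 1,800 + 2,000 = 19,500.
- r = 25% referred, and 50% of those referred enroll (Participants).
- d = share of smokers with a reminder display. Not given.
- s = share of referred smokers with no reminder display. Not given.

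**Step 3. The plan's own figure.** 19,500 × 0.25 = 4,875 referrals, and 4,875 × 0.50 = 2,437.5 enrolled, against a stated total of about 2400. It reproduces. No expected value of Reach is stated.

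**Step 4. Shortfall in Reach.** As written, Reach = d. Counting every referral as exposure, Reach = d + min(s × r, 1 − d). The shortfall is therefore min(s × r, 1 − d), which is at most s × r:

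- s = 0: no shortfall.
- s = 10%: 0.10 × 4,875 = 487.5 smokers; 0.10 × 25% = 2.5 points.
- s = 25%: 0.25 × 4,875 = 1,218.75 smokers; 6.25 points.
- s = 50%: 0.50 × 4,875 = 2,437.5 smokers; 12.5 points.

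The cap matters when display is common. At d = 60% and s = 50%, Reach moves from 60% to 72.5%. At d = 90%, only 10% of smokers (1,950) have no display, so s = 50% cannot apply in full and the shortfall is limited to 10 points. The percentage-point bounds depend on r and s only, not on the 19,500.

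**Step 5. Does another outcome fill the gap?** Patient adoption divides enrolled patients by referred patients, and treatment uptake in Table 4 uses the same base. The Table 4 referral rates for patients are counts. No named outcome gives referred or enrolled smokers over all smokers with a visit.

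**The case against.** The strongest reply is that the Reach section makes a deliberate and complete choice. RE-AIM is introduced for a system-level intervention, the program begins with a change to the provider's electronic record, and use of the program is counted separately under Adoption. On that scheme a reminder that the provider ignores is low adoption, not false reach. This stands. Display is a defensible measure of exposure to the system change, and requiring patient contact would be a preference between definitions. The figure only needs to be labeled as exposure to the program.

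It is also true that the rule tests display and not the route of referral. A reader might infer that every referral by menu, template or email is lost. The documents do not support that: such a patient still counts as exposed if the reminder appeared. Because the common record system carries tobacco reminders and screening is required, patients with no display may be few.

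A reader might also infer that Reach is overstated four- to eight-fold, by setting a display rate near 100% against planned referral of 25% (100/25 = 4) and enrollment of 12.5% (100/12.5 = 8). That does not hold either. Exposure and uptake are different quantities, exposure is expected to be the larger, and no display rate is given.

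Finally, Table 4 is a compressed schedule of formative measures, and the Reach section holds the full definition. Brevity may explain the looser denominator. It does not explain naming a different event.

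**Conclusion.** The point holds in two parts. First, the article gives exposure to TeleQuitMH two numerators, and the one in Table 4 is a usual-care event that does not show exposure to the program. This is plain from the text and needs no assumption. Second, the Reach rule can class a referred or enrolled smoker as not reached. How often is unknown. If 10% to 50% of the planned 25% referred had no display, the understatement is at most 2.5 to 12.5 points, and less where display is so common that little room remains. That range rests on an assumed share; it is not an estimate.

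The matter should be corrected, but its reach is limited. It concerns a descriptive implementation outcome and does not touch abstinence, the randomized Aim 3 comparison or its power.

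**What to change.** - Use one definition in the Reach section and in Table 4. The denominator is all smokers with a mental health visit in the intervention period. A smoker in that group is exposed if the adapted reminder was displayed or if any TeleQuitMH referral was made, whether by reminder, consult menu, assessment template or email.
- Rename the present Table 4 row as a tobacco screening measure.
- Label the Reach figure as exposure to the program, and report referred and enrolled smokers over the same denominator beside it.

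The cost is a change of wording and a small merge of the lists of referred and enrolled patients (planned under Adoption) with the record extract (planned under Reach). Email referrals will need matching to that extract by patient. No new data collection is needed.
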